Aim 2 will evaluate CACP effectiveness (compared to usual care) and implementation outcomes using mixed methods. The primary effectiveness outcome is the number of days alive out of ED or hospital within 30 days of the day following randomization, ascertained by EHR review; this outcome includes all unplanned hospitalizations, ED visits, and deaths, which will also be assessed separately as safety endpoints. This primary outcome measure was selected for its relevance to the desired goal of the CACP program, i.e., shortening and/or preventing ED and hospital utilization. It captures both the initial impact of CP services availability and the effectiveness of the program in meeting the needs of the patient and preventing the return to the ED/hospital subsequent to initial discharge. Planned hospital stays will be excluded from the primary outcome. The secondary outcomes include the proportions of patients experiencing the components of the primary outcome (i.e., percent of patients with unplanned hospitalizations, ED visits, and death), the rates of each component of the primary outcome, the proportion of patients requiring SNF care, as well as patient-reported health-related quality of life (HRQoL) and treatment burden using the patient-reported EQ-5D [19] and PETS [20] measures. For patients in the CACP program, patient satisfaction will also be evaluated. Implementation outcomes, organized by the RE-AIM implementation evaluation framework (Reach, Effectiveness, Adoption, Implementation, and Maintenance), as shown in Table 2, will be ascertained using administrative and EHR data and interviews. Reach and adoption outcomes include metrics for the eligible population, while other implementation outcomes are specific to the intervention group. Additional secondary analyses will assess for the heterogeneity of treatment effects as a function of baseline ED/hospital utilization, source of referral, reason for referral, services delivered, patient demographics (age, sex, rurality, race/ethnicity, limited English proficiency, area-level deprivation), number of CP visits, and duration of CP care. Sensitivity analyses will be performed excluding hospice deaths and utilizing the per-protocol rather than the intention-to-treat approach.

Aim 3 will assess acceptability/satisfaction and perceived sustainability using surveys [21] and interviews with patients, CPs, clinicians and other members of the health care team, and administrators.

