#### Sample size {14}

For aim 1, the sample size will be assessed iteratively during data collection and analysis with the aim of ensuring that the implementation plan is feasible and meets the needs of key user groups. We anticipate up to 25 interviews in the pre-implementation phase for aim 1.

The aim 2 sample size was calculated on the basis of the primary hypothesis. Pilot studies of CP care on days out of ED or hospital in the first 30 days yielded an estimated mean of 27 days in the intervention group. A difference of 2 days was considered clinically important by stakeholders. We have powered this trial to detect a 10% improvement in the primary outcome. To detect a mean difference of 2 days out of ED or hospital at 30 days with a two-sided significance level of 0.05 and a power of 80% with equal allocation to two arms would require 120 patients per group assuming a pooled standard deviation of 5 days. The standard deviation was estimated by assuming the range of measurement will span approximately six standard deviations. Because the primary endpoint is assessed at 30 days and based on the coverage of the EHR, we expect minimal drop-out and missing data. Multiple imputation will be used if more than 20% of patients have missing data on the primary outcome. Aim 3 qualitative inquiry will use a purposeful sampling approach to intentionally select participants who can provide information about their experiences with the program. Based on the past experience of this team, the heterogeneity of expected patient situations, and the scope of this inquiry, we anticipate conducting approximately 25 patient interviews. We anticipate up to 35 clinicians and other stakeholders will also complete aim 3 interviews.

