## Statistical methods

### Statistical methods for primary and secondary outcomes {20a}

#### Aim 1

We will use methods of rapid qualitative analysis, guided by constructs in the Consolidated Framework for Implementation Research (CFIR) [22]. Members of the study team will meet to review notes and audio recordings from interviews and discuss issues that may impact implementation, including those that should be addressed before trial enrollment commences. Notes will be summarized in a template guided by the CFIR framework and imported into qualitative software (NVivo, QSR International) for data management. Summaries will be presented at biweekly study team meetings for discussion of potential actions, including changes to the implementation plan.

#### Aim 2

The main analysis of the primary outcome will be based on the intention-to-treat (ITT) principle, with all patients randomized to CACP compared to all patients randomized to usual care. The ITT sample will comprise all patients who were randomized and completed the baseline assessment. The primary outcome (CACP effectiveness) is defined as the number of days the patient was alive and outside of the ED or hospital (excluding planned hospital admissions for scheduled surgeries, procedures, and/or treatments). Outcomes will also be analyzed in the per-protocol subset. The per-protocol sample will comprise all patients in the ITT arm except for those who did not follow protocol, i.e., patients who did not receive CP services in the intervention arm.

The mean number of days out of the ED or hospital for the intervention group will be compared to that of the control arm. Statistical significance, and a two-sided confidence interval for the difference between arms, will be assessed by using the two-sample *t* test. The distributional assumptions for the test will be assessed by calculating the skew and kurtosis for the bootstrap distribution of the sample difference between means. The Hodges-Lehman shift estimator for the Wilcoxon rank-sum test will be used if the absolute value of the skew or kurtosis-minus-three are greater than 1.5.

Other continuous outcome measures will be assessed by the same method as the primary outcome measure. Categorical measures will be assessed by using the Pearson chi-square test, or the Fisher exact test will be used if the minimum expected cell count is less than five.

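### The switch from the t test to Hodges-Lehmann rests on a threshold that the tested quantity cannot reach, so the stated safeguard against non-normality does not operate

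*Protocol article*

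**What the plan says.** Under Statistical methods for primary and secondary outcomes {20a}, Aim 2, the protocol article sets the comparison: "The mean number of days out of the ED or hospital for the intervention group will be compared to that of the control arm". Significance and the confidence interval "will be assessed by using the two-sample *t* test". The assumptions of that test are to be checked by "calculating the skew and kurtosis for the bootstrap distribution of the sample difference between means". The fallback follows: "The Hodges-Lehman shift estimator for the Wilcoxon rank-sum test will be used", on the condition that it "will be used if the absolute value of the skew or kurtosis-minus-three are greater than 1.5". The same section extends the procedure: "Other continuous outcome measures will be assessed by the same method as the primary outcome measure".

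Two other sections bear on the fallback. Outcomes {12} defines the primary outcome as "the number of days alive out of ED or hospital within 30 days of the day following randomization", a count with a ceiling at about 30. Sample size {14} reports that pilot work "yielded an estimated mean of 27 days in the intervention group" and powers the trial on a 2-day difference in means, with 120 patients per group.

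**The concern.** The check is applied to a resampled difference in means, not to patient-level data. Averaging pulls skew and excess kurtosis towards zero, and a cut of 1.5 may be one that no trial data can pass. The protocol would then promise protection against a badly behaved distribution and provide none. The outcomes that inherit the rule would be affected too, and some of those may have fewer usable observations than the primary.

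The fallback raises a second matter. Hodges-Lehmann estimates the median of all pairwise differences between arms. The trial is powered on a difference in means. With a ceiling at about 30 days and an expected mean of 27, skew and ties are likely, and the two quantities can then differ a good deal.

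**Working it through.** **Inputs.** From the protocol article: the object checked (bootstrap distribution of the difference in means), the cut (1.5 for absolute skew or absolute kurtosis minus 3), 120 per group, the 30-day window, the intervention mean of 27 and the 2-day target. The article gives no derivation for 1.5, so there is no figure to reproduce. The bounds below hold at any sample size, so they do not depend on how the 120 was obtained.

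**Step 1: one arm.** Let a sample of n have skew g1 and excess kurtosis g2. Its bootstrap mean has
- skew = g1/√n
- excess kurtosis = g2/n

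For any n numbers whatever, |g1| ≤ (n−2)/√(n−1), and g2 lies between −2 and n−5+1/(n−1). So
- |skew of bootstrap mean| ≤ (n−2)/√(n(n−1))
- −2/n ≤ excess kurtosis of bootstrap mean ≤ (n−5+1/(n−1))/n

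| n per arm | max absolute skew | max excess kurtosis | min excess kurtosis |
|---|---|---|---|
| 10 | 0.843 | 0.511 | −0.200 |
| 30 | 0.949 | 0.834 | −0.067 |
| 120 | 118/√(120×119) = 0.987 | (115+1/119)/120 = 0.958 | −0.017 |
| 1,000 | 0.998 | 0.995 | −0.002 |

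Over every n from 2 to 100,000, no absolute value exceeds 1.

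**Step 2: difference between arms.** Let w be one arm's share of the variance of the difference. With independent resampling within arms,
- skew of difference = w^1.5 × skew_A − (1−w)^1.5 × skew_B
- excess kurtosis of difference = w² × kurt_A + (1−w)² × kurt_B

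Because w^1.5 + (1−w)^1.5 ≤ 1 and w² + (1−w)² ≤ 1, neither can exceed the larger arm value in absolute terms. The bound of 1 carries over.

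**Step 3: worst case at 120 per arm.** One patient at 0 days and the other 239 at 30 gives skew −0.987 and excess kurtosis 0.958. If both arms are pooled and resampled together, so that arm sizes vary, the same data give about −1.00 and 1.05 by simulation. Both are still well short of 1.5.

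**Step 4: plausible data.** With simulated outcomes capped at 30 and 120 per arm (1,000 trials per scenario), the largest values were about 0.16 for skew and 0.05 for excess kurtosis.

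**Step 5: finite resampling.** The bound is for the bootstrap distribution itself. An estimate from a limited number of resamples can stray above 1.5 by chance. In the worst case of Step 3 this happened in about 11% of runs at 1,000 resamples and 0.2% at 10,000. It needs data that are almost all one value.

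**Step 6: does the retained t test hold up?** In simulated capped outcomes at 120 per arm (5,000 trials per scenario, shapes assumed), with raw skew of −2.0, −2.3, −2.6 and −4.4, type I error was 4.9%, 5.1%, 4.4% and 4.4%. Confidence interval coverage was 95.6% under a difference of about 1.9 days.

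**Step 7: what the fallback would estimate.** The protocol does not state the share of patients at 30 days, so these shares are assumptions. Simulations used 120 per arm.

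| At 30 days, CACP / usual care | Mean difference | Average Hodges-Lehmann |
|---|---|---|
| 50% / 10% | 1.93 | 1.78 (never 0) |
| 50% / 25% | about 2 | 1.19 |
| 30% / 20% | 1.96 | 1.06 |
| 50% / 40% | 1.98 | 0.23 (exactly 0 in 78% of trials) |
| 60% / 55% | 1.73 | 0.00 (exactly 0 in all trials) |

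**The case against.** The strongest reply is that an inert switch does no damage. If it never fires, the result is always the t test on mean days, which is the quantity the protocol compares and powers. Step 6 shows that this test behaves well at 120 per arm, even with heavy skew. That stands.

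A reader might infer that the estimand of the primary analysis is left open, or that the reported effect could shrink by more than half. The document does not support that. Both would require the switch to fire, and the text ties the cut explicitly to the bootstrap distribution. An analyst would have to misapply it to raw data, or someone would have to lower the threshold later.

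Nor can the fallback be said to give a result near zero as a matter of course. Intervention description {11a} expects most usual-care patients to go to the ED and hospital or to other care pathways. Many controls may therefore lose days and not tie at 30, and Step 7 then gives a value close to the mean difference.

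The reach to secondary outcomes is also limited. The extension covers continuous measures; categorical ones go to chi-square or Fisher tests. Duration of SNF stay is listed as exploratory, and no error rate for a sparse outcome was calculated here.

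None of this rescues the rule. A decision threshold that cannot be reached is wrong as written.

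**Conclusion.** The concern holds in a limited form. The 1.5 cut cannot be reached by the quantity it is applied to: the ceiling is 1 at any sample size, and 0.987 and 0.958 at 120 per arm. This is algebra and needs no assumption about the data beyond resampling within arms. The only exception is simulation noise in near-constant data. The stated check on distributional assumptions is therefore empty, for the primary outcome and for the other continuous outcomes.

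It would be going too far to conclude that the primary analysis is invalid. Read literally, the plan always keeps the t test, which is adequately calibrated at the planned size under the assumed shapes.

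The choice of fallback is a conditional weakness. If the cut were misapplied to raw data, or repaired by lowering it, the estimate would move from the powered mean difference to a different quantity, averaging from 0 to about 1.8 days in simulations with mean differences of about 1.7 to 2 days. That range rests wholly on the assumed shares at 30 days. The text should be corrected before analysis, but the trial's conclusion does not hang on it.

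**What to change.** Delete the switch. State that the difference in mean days is the estimand for the primary outcome whatever the shape of the data. Give a confidence interval and p-value that respect the six randomisation strata, for example from a linear model with stratum terms, or from a stratified bootstrap with a within-stratum permutation test. Using the strata is a small gain and not a rescue: in one assumed scenario with stratum effects, a t test that ignored them had 4.0% type I error, against 5.1% for inference within strata.

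Report any rank-based result only as a labelled sensitivity analysis, and apply the same rule to the other continuous outcomes.

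The cost is two sentences in the analysis section and a little extra code. Sample size and trial conduct are unaffected. The article places quantitative analysis at the close of the study, so the change can be made before results are seen.

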### Data collection and management

#### Plans for assessment and collection of outcomes {18a}

Participants randomized to CACP will have access to CP services ordered and overseen by the treating clinical team per the current standard of care. Thus, the clinical trial evaluates the CACP care delivery model rather than the clinical care that is provided to patients within it. Participants randomized to usual care will not have access to CP services and will continue with their care as planned by the treating clinician(s).

All participants will complete a baseline survey at the time of enrollment/consent and at 30 days. Participants randomized to CACP will also complete a survey after their last CP encounter. Paper copies of the baseline surveys will be completed at the time of enrollment or provided to the participant and returned by mail. In the CACP treatment arm, we will ask that baseline surveys be completed and returned before or during the first CP visit. In the usual care arm, for participants who did not complete their baseline survey at the time of enrollment, up to 3 reminder phone calls will be made by a member of the research team to participants who have not returned their survey by the end of week 1.

Participants randomized to the CACP treatment arm will also be asked to complete a survey after their last CP visit. This survey will be handed to the participant by the CP at their last visit with a pre-stamped envelope so it can be completely private and returned by mail or sealed and given to the CP for delivery. If participants need help completing the survey, the research team study coordinator will contact them by telephone and complete the survey with them. Patients in the intervention arm who are recruited and consent to participate in an interview will complete it by telephone with a trained member of the study team unaffiliated with intervention delivery. Interviews will be audio-recorded with permission and transcribed for analysis.

Patients in both arms will be asked to complete a paper survey at day 30, administered between days 30 and 40 (first attempt) and with all 3 contact attempts completed by day 90. If participants need help completing the survey, it can be done over the phone with the research team study coordinator.

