Sensitivity analyses concerning the primary and secondary endpoints will be conducted, including excluding hospice deaths, examining the impact of the number of CP visits, examining the impact of the duration of CP care (< 10 days, 10–19 days, 20–29 days) and per protocol vs ITT. The impact of covariates will be assessed by using multiple linear regression or multiple logistic regression.

Descriptive statistics and figures will be provided as appropriate for secondary outcomes, and baseline demographics will be summarized for each arm. Validated instruments (e.g., EQ-5D) will be scored per official guidance, and the results will be reported as appropriate. When data is available, changes in rates or scores between baseline and 30 days will be reported for each arm along with comparisons between the groups. Implementation outcomes will be summarized using descriptive statistics.

#### Aim 3

Qualitative data will be analyzed following qualitative content analysis procedures, guided by the theoretical constructs employed in the study. Analysis will begin with at least two members of the study team reviewing audio files and transcripts. A coding framework will be developed, starting with a priori topics in the interview guide and constructs from theoretical frameworks like CFIR. Analytic memos will be used to summarize the findings, including any key differences by participant role.

Surveys will be analyzed using descriptive statistics and scoring guidance for validated instruments (e.g., CSAT). Integration of findings will involve a comparison of quantitative and qualitative findings by construct, e.g., survey and interview data on acceptability and sustainability.

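### EQ-5D and PETS are collected at baseline, but the planned day-30 comparisons do not adjust for the baseline score and so give up precision on these secondary outcomes

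*Protocol article*

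**What the plan says.** All references are to the protocol article.

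- **Data.** Under Plans for assessment and collection of outcomes {18a}: "All participants will complete a baseline survey at the time of enrollment/consent and at 30 days". Table 3 schedules EQ-5D and PETS at allocation and at 30 days.
- **Test.** Under Statistical methods for primary and secondary outcomes {20a}, Aim 2, the difference in the primary outcome "will be assessed by using the two-sample *t* test". A Hodges-Lehmann/Wilcoxon fallback applies if skew or kurtosis limits are exceeded. Then: "Other continuous outcome measures will be assessed by the same method as the primary outcome measure". Neither the t test nor the fallback uses the baseline score.
- **Change.** Later in the same section, where data are available, "changes in rates or scores between baseline and 30 days will be reported for each arm along with comparisons between the groups".
- **Adjustment.** One sentence there says that the impact of covariates will be assessed by multiple linear or logistic regression. It follows the sensitivity analyses, names no covariate and does not mention the baseline score.
- **Timing of baseline.** Section {18a} asks CACP patients to return the baseline survey before or during the first paramedic visit. Usual-care patients who have not returned it by the end of week 1 get reminder calls. Some baseline scores can therefore be obtained after allocation, on schedules that differ by arm.

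**The concern.** A patient's baseline score usually predicts the same patient's day-30 score. An analysis of day-30 scores alone leaves that predictable variation in the error term. An analysis of raw change subtracts the whole baseline score, which over-corrects when the correlation is modest. A model that estimates the slope on baseline avoids both faults.

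At stake is the width of the confidence intervals for quality of life and treatment burden, the only patient-reported scales compared between the arms. A smaller matter is that two between-arm estimates per scale are mentioned and neither is named as the result. A chance baseline imbalance of size D moves the day-30 difference by rho × D and the change difference by −(1 − rho) × D, so the two are pulled in opposite directions.

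**Working it through.** **1. The plan's own figure.** The document gives no sample size, SD, target difference or correlation for EQ-5D or PETS. Its only calculation, under Sample size {14}, is for the primary outcome. The target is a 2-day gap between the arm means, tested at two-sided 5% with 80% power and 1:1 randomization; the article says this "would require 120 patients per group assuming a pooled standard deviation of 5 days". The inputs give n = 2 × (1.960 + 0.842)² × 5²/2² = 98.1, so 99 per group (100 with the t distribution). The stated 120 is not reproduced, and 120 per group gives about 87% power. That mismatch is a separate matter. The number 120 is used below only as an upper bound on survey completers per arm, and the variance ratios do not depend on it.

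**2. Variance of the arm difference.** Assume the same SD at baseline and day 30, correlation rho, and a usable pre-allocation baseline for everyone. Relative to the day-30 t test:

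- day-30 t test: 1
- raw change: 2(1 − rho)
- baseline-adjusted model: 1 − rho²

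The smallest difference detectable with 80% power at 120 per arm, in SD units, is (1.960 + 0.842) × √(2/120 × factor).

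| rho (assumed) | Variance: t test / change / adjusted | Saving of adjusted over t test | Detectable difference: t test / change / adjusted |
|---|---|---|---|
| 0.3 | 1 / 1.40 / 0.91 | 9% | 0.362 / 0.428 / 0.345 |
| 0.5 | 1 / 1.00 / 0.75 | 25% | 0.362 / 0.362 / 0.313 |
| 0.7 | 1 / 0.60 / 0.51 | 49% | 0.362 / 0.280 / 0.258 |

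The adjusted model beats both planned analyses for any rho strictly between 0 and 1. At rho = 0 it ties with the t test. With equal SDs, raw change is less precise than the t test below rho 0.5 and more precise above it.

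**3. Incomplete pre-allocation baselines.** If a share p of patients has a usable baseline and the rest receive one imputed value plus an indicator, the factor is about 1 − p × rho². With p = 0.5 (assumed):

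- rho 0.3: 1 − 0.5 × 0.09 = 0.955, a saving of 4.5%
- rho 0.5: 1 − 0.5 × 0.25 = 0.875, a saving of 12.5%
- rho 0.7: 1 − 0.5 × 0.49 = 0.755, a saving of 24.5%

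**4. Power, for illustration only.** Borrow the primary outcome's standardized effect, 2/5 = 0.4, with 120 per arm. The t test then has 87.0% power. The adjusted model has 89.9% at rho 0.3 and 94.6% at rho 0.5 with complete baselines, or 88.4% and 91.0% with half.

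**5. If both unadjusted comparisons were treated as tests.** In a simulation of 100,000 trials per setting (120 per arm, rho 0.3 to 0.7, no true effect), they disagreed on significance in 7.5% to 8.7% of trials. At least one was significant in 8.7% to 9.3%.

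**The case against.** - **Nothing here is invalid.** Under randomization the day-30 t test is unbiased whatever the baseline does, and these are secondary outcomes for which the trial was not sized. This stands. A reader might infer that the planned analyses are biased, but the document does not support that for the t test, nor for the change score when baseline precedes allocation.
- **The power gain is borrowed.** The 0.4 effect belongs to days out of the ED or hospital, and rho is assumed. Baselines are taken around an acute episode, so a low rho is plausible, and the SDs need not be equal. This stands, so the point rests on variance ratios over a range and not on a claimed gain in power.
- **Baseline timing is unreliable.** The survey rules in {18a} allow baselines after allocation, which reduces the gain. This stands, and it is the main limit on the benefit. It does not favour the planned change score, which uses the same late baselines.
- **Adjustment may already be intended.** The covariate sentence could cover it, and a covariate list may sit in a fuller document. But the article itself fixes the unadjusted t test for these scales, and that sentence neither names the baseline score nor displaces the test.
- **Two rival results?** A reader might infer that each scale has two competing confirmatory answers. That goes too far. The change comparison is conditional on data being available and sits in a mainly descriptive paragraph. Table 1 does list both T3 and the span from the day after randomization to T3 for these scales, but the safety row uses the same wording for events, so it does not establish a change-score test. What remains is that between-group comparisons of change are announced and no lead estimate is named.

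**Conclusion.** The point holds as an improvement in precision for secondary outcomes, with a smaller need to name the lead estimate. The planned comparisons of EQ-5D and PETS leave a measured baseline score unused, or use it with a fixed slope of 1.

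Against the t test, adjustment saves 9% to 49% of the variance for rho from 0.3 to 0.7 with complete baselines, and roughly half as much if only half the patients have a usable one. These figures assume equal SDs at the two time points; rho and the usable share are not in the document. At rho 0.3 the gain is modest. The evidence does not support a claim of bias, of inadequate power for these scales, or of a gain at every correlation: at rho = 0 the t test loses nothing.

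**What to change.** In Statistical methods for primary and secondary outcomes {20a}, Aim 2, replace the carry-over of the primary method for these scales with a statement along these lines: the main between-arm result for EQ-5D and for each PETS domain is the adjusted difference from one linear model of the day-30 score on arm and the baseline score, with robust standard errors. Only baseline scores obtained before allocation enter as the covariate. Patients without one are kept by a single imputed value, the same in both arms, and a missing indicator. Unadjusted means and change scores are reported as description only.

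Restricting the covariate to pre-allocation scores matters: whether a score is available is then settled before the arm is known, which keeps the imputed value and indicator from introducing bias.

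The cost is a few sentences, with no new data and no extra patients. The downside is the work of dating each baseline survey and handling missing or late ones, which also reduces the gain.
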